**Research Proposal****Muscle-Related Side Effects of Statins: Functional Impact, Mechanisms, and Potential Reversibility with Vitamin D Supplementation****1.0 PROJECT OVERVIEW**

Amongst the most prescribed drugs worldwide, statins play a key role in health care by improving the cardiovascular outcomes of many patients. However, the use of statins is not without side effects. Besides the rare cases of rhabdomyolysis, other skeletal muscle-related side effects (MRSE) such as myalgia, cramps, and fatigue are estimated to affect 10% or more of the patient population under statin treatment [1]. Because approximately 10% of the population is taking statins on a daily basis [2], we can then extrapolate that over 300,000 Canadian patients are suffering from MRSE. Surprisingly little is known about the functional impact of these symptoms or the mechanisms responsible for their appearance. More importantly, health care professionals do not know how to deal with or relieve patients from MRSE. This unique project fills in this knowledge gap by combining functional, histological, and molecular approaches to improve our understanding of skeletal muscle-statin interactions and by testing an alternative treatment to reduce MRSE.

**Objectives:** The two main objectives of this study are the following:

- 1) To test muscle strength and fatigability and investigate skeletal muscles at the histological and molecular levels in statin treated patients with and without MRSE; and*
- 2) To assess the usefulness of vitamin D supplementation in improving muscle function and structure and reducing muscle-related side effects.*

More specifically, this project will enable us to determine (1) whether a loss of muscle strength and endurance can result from statin treatment, (2) whether statin therapy influences muscle morphology (in particular mitochondrial content and function) and increases muscle fiber degeneration in some susceptible subjects in relation to functional changes, and (3) if vitamin D supplementation can decrease statin-induced MRSE and muscle tissue damage while preserving muscle function and the cardiovascular benefits (decreased low-density lipoprotein cholesterol levels) of the drug.

**Hypotheses:** 1) Patients under statin monotherapy and suffering from statin-induced MRSE show reduced muscle strength and increased fatigability associated with an increased prevalence of cell damage, proteolytic markers, and perturbed mitochondria. 2) The cessation of statin monotherapy improves muscle function and reduces biological markers of muscle cell degeneration in patients with MRSE. 3) Vitamin D supplementation followed by statin reintroduction protects against statin-induced MRSE.

**Patient population:** Men and women aged between 30-60 years (inclusive) and affiliated with the cardiovascular prevention lipid clinic at the Laval University Hospital Research Centre (CHUL) will be included in this study. Patients treated with statin therapy for the first time in the last year with or without MRSE and with normal creatine kinase (CK) blood levels will be recruited. These patients must not have taken statins or lipid-lowering drugs before the last year or consume vitamin D supplements. MRSE must clearly have begun after statin introduction. These patients will be in low cardiovascular risk primary prevention, allowing us to modify their lipid-lowering drug regimen for a short period of time.

**Impact:** A better understanding of the cellular and molecular events leading to muscle pain, damage and dysfunction in the presence of statins is essential for the design of effective therapeutic modalities. We are convinced that this project will provide the basic foundation for this and may position Canada as a world leader on how to deal with MRSE associated with statins. Lastly, the present proposal also proposes an alternative treatment by testing the combination of statins and vitamin D supplementation to alleviate MRSE, an area in which clinical research and transferable solutions to patients are crucially needed.

**Research Proposal****2.0 BACKGROUND AND RATIONALE**

HMG-CoA reductase inhibitors (statins) are effective and popular agents for reducing circulating LDL-cholesterol levels in both primary and secondary prevention of cardiovascular disease. In the last decade, there have been over 500 million prescriptions for statins dispensed in developed countries. The use of statins is expected to increase in Canada over the next few years, as the patent protection period for most major statins is expiring and cheaper generic versions come to market. For example, Pfizer's Lipitor (atorvastatin), the world's best selling medicine (sales nearing US\$11.5bn globally in 2009, about US\$1.2bn in Canada alone), will be facing competition from Apotex (Canada), Teva Pharmaceutical Industries (Israel), Watson Pharmaceuticals (US) and Ranbaxy Laboratories (India), who have all announced the launch of their atorvastatin products in Canada on the back of product approvals by Health Canada. Furthermore, the most recent Canadian guidelines [3] for the diagnosis and treatment of dyslipidemia and prevention of cardiovascular disease in the adult have broadened the inclusion criteria for pharmacological treatment as well as targeted even lower plasma LDL levels. Taken together, the patient population with prescribed statins in Canada is expected to increase significantly within the next few years and a better understanding of statin-induced MRSE is therefore very relevant for the Canadian population.

**Statin-induced myopathy.** Statins are generally well tolerated and very serious side effects appear to be rare [4]. The one notable serious adverse reaction to statin therapy is *rhabdomyolysis* (muscle symptoms with marked creatine kinase elevation and creatinine elevation [4]), which was observed early on with lovastatin in cardiac transplant patients [5]. In the worst cases, severe myoglobinuria accompanied by serum CK levels greater than 10 times normal, acute renal failure and even death can occur. Only a small fraction of patients who are treated with statins will develop such a severe myopathy (perhaps 1 in 10,000 patients) [6]. Based on FDA reports, the rate of fatal rhabdomyolysis was 16- to 80-fold greater for cerivastatin as compared to other statins, particularly at higher doses, but the mechanisms leading to such muscle toxicity are still poorly understood. In clinical practice, some non-specific predisposing factors have been pointed out and included advanced age, low body weight, female gender, use of multiple medications, multi-systemic disease, acute illnesses and major surgery [4]. Information on these issues as well as on the confusing area of low-grade myopathy (with normal CK) associated with statin use remains, however, extremely limited.

In addition to these rare but potential lethal cases of rhabdomyolysis, anecdotal and empirical observations indicate that other MRSE can result from statin use, including *myalgia* (muscle ache or weakness without elevated creatine kinase levels [4]), cramps, and reduced exercise endurance. These MRSE are generally believed to be more common than reported in statin clinical trials, in part because these studies were not designed to assess these particular symptoms. For example, a recent observational study of nearly 8,000 patients under high dose statins in primary care showed that 10% of patients presented MRSE, a prevalence that reached 16% for some statins [1]. These MRSE can be relatively severe and are an important quality of life issue, the pain often sufficient to alter the patients' normal physical activities. They can also lead to statin therapy cessation, preventing patients from achieving LDL cholesterol goals at any cardiovascular risk level. Furthermore, statin use may exacerbate muscle performance declines with impacts on health; *e.g.*, their use is associated with an increased risk of falls with aging without a concomitant decrease in muscle mass, an effect that may be reversible with statin withdrawal [7].

Although most studies have focused on middle-aged or older adults (typical of the statin-prescribed patient population), statin-related MRSE are not limited to older adults. In a study of young (24±6 yrs) professional athletes (15 men, 7 women) suffering from familial hypercholesterolemia, all ceased statin therapy due to myalgia. After withdrawal, all MRSE symptoms disappeared [8].

The impact of statin-induced MRSE on medication compliance is unknown. The persistence and adherence to medications that must be taken chronically are rather low. In fact, less than half of patients

---

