### 3.0 STUDY DESIGN AND EXPECTED FINDINGS

A flow diagram summarizing the study design and an outline of patient participation can be found in **Figure 1** and **Table 1**.

[figure not shown]

**Figure 1:** Simplified timeline and flow diagram of proposed study. Q1, Q2, and Q3: questionnaires; Exam: physical examination (including anthropometry) and blood work; FT: functional muscle testing; Bx: *vastus lateralis* muscle biopsies (in a subset of patients).

**Table 1:** Subject population breakdown in proposed study. Subjects from objective #1 will be randomized into experimental (vitamin D) and control (placebo) groups for objective #2 based on age, sex, MRSE and 25(OH)D levels.

| Group                      | Objective #1          | Objective #2                                                     |
|----------------------------|-----------------------|------------------------------------------------------------------|
| Statin taking with MRSE    | 60 (20 with biopsies) | 30 vitamin D (10 with biopsies)
30 placebo (10 with biopsies) |
| Statin taking without MRSE | 30 (10 with biopsies) | 15 vitamin D (5 with biopsies)
15 placebo (5 with biopsies)   |
| Controls (no statins)      | 10 (5 with biopsies)  | —                                                                |

**Inclusion criteria:** Healthy and sedentary or moderately physical active (less than 1 hour of leisure-time physical activity per week) men and women aged 30 to 60 years (inclusive). Patients placed on statin therapy for the first time in the last year with or without MRSE and with normal CK blood levels.

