**Functional assessment and blood samples**

A case-control approach will be used to compare patients under statin treatment with and without MRSE. After initial testing while under statin treatment, statin treatment will be stopped for 2 months followed by retesting. Recent studies have shown that most statin MRSE as well as structural muscle damage appearance/disappearance occurs within a two month period of statin introduction/withdrawal [1, 13]. A control group of 10 statin-naïve patients will also be included for test-retest variability assessment of all parameters.

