Following screening, 60 patients presenting MRSE (assessed by a standardized questionnaire; see **Appendix 3, questionnaire 3**) under statin monotherapy (any statin, any dosage) as well as 30 patients without MRSE under statin monotherapy (paired for statin and dosage with the MRSE cohort) will be evaluated. Muscle strength and fatigability will be tested by standardized procedures before and after two months of stopping statin monotherapy. Briefly, strength of the extensors and flexors muscles of the dominant leg will be quantified with a Biodex isokinetic dynamometer available in our research centre. Forces will be tested during 3 reps at 60 and 180 deg/sec and endurance during a 15 reps test at 180 deg/sec. These tests will be preceded by a 5 reps warm-up at 60 deg/sec including one movement at maximal voluntary contraction [46]. Each maximal concentric contraction will be performed in the first 90 degrees of the knee range of motion. Patients will sit in an upright position and mechanical axis and resistance pads will be aligned according to the manufacturer's guidelines. The results will be reported in Newton-meters (Nm). Peak torque, rate of torque development and total work values will be obtained following these isometric and isokinetic measurements. These groups of muscles were selected because muscle weakness or myalgias with statins are most frequently localized in lower limbs. Handgrip strength of the dominant hand will also be tested in a static mode with a Jamar dynamometer (best of 3 repetitions). These testing procedures are well standardized, easy to perform and very reproducible, and are routinely used in the department of physical therapy at our centre. Test-retest variability for the Biodex measurements is shown to be within  $\pm 15\%$  [46], which our personal experience confirms. The primary efficacy parameter will be the percent change for these measurements from baseline to end of each phase of the study.

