**Research Proposal**

---

Subjects (see **APPENDIX 1, Table 1**) in our study were statin users and had muscle side effects (cramps, myalgia, reduced muscle endurance) evaluated with our in-house questionnaire (see **APPENDIX 3, questionnaire 3**). All subjects were in primary cardiovascular prevention. Different statins were used by different participants, the majority at low doses (the highest being 20 mg).

After statin withdrawal, all subjects reported important decreases in the level of pain experienced (**APPENDIX 1, Figure 1**), and 70% showed functional improvements in at least one Biodex measure of muscle performance (**APPENDIX 1, Figure 2**). On average, the strength of the extensor and flexor muscles increased by  $22\pm 43\%$  and  $17\pm 28\%$  respectively, power by  $28\pm 64\%$  and  $29\pm 41\%$ , and endurance by  $28\pm 57\%$  and  $20\pm 35\%$  (means $\pm$ SD). No effects were observed on blood CK and AST values (**APPENDIX 1, Table 2**).

Our preliminary results show that cessation of statin therapy increased muscle functional capacity in the majority of subjects who experienced *a priori* muscle discomfort. ***Since this condition could affect the pharmacological compliance and potentially modify the cardiovascular benefits of statins, it is imperative to better characterize this dysfunction and develop approaches to reduce its impact.***

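### Objective 1 limits leisure activity only at entry, on statin, and shows no record of it up to the retest 2 months off statin, so reconditioning cannot be separated from a direct statin effect on muscle

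*Protocol*

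**What the plan says.** - **Pain and activity.** Protocol section 2.0, Statin-induced myopathy, says of MRSE: "the pain often sufficient to alter the patients' normal physical activities".
- **Entry limit.** Section 3.0, Inclusion criteria, admits: "Healthy and sedentary or moderately physical active (less than 1 hour of leisure-time physical activity per week) men and women". The statin patients are on drug when they meet it: "Patients placed on statin therapy for the first time in the last year with or without MRSE and with normal CK blood levels".
- **Contrast.** Objective 1, Functional assessment and blood samples: "After initial testing while under statin treatment, statin treatment will be stopped for 2 months followed by retesting". The same part of the protocol states: "The primary efficacy parameter will be the percent change for these measurements from baseline to end of each phase of the study".
- **Comparators.** The 30 patients without MRSE are paired with the MRSE cohort on statin and dosage. The 10 statin-naive controls serve to assess test-retest variability.
- **Pilot.** Under Preliminary data, after withdrawal "all subjects reported important decreases in the level of pain experienced".
- **Questionnaires.** Section 4.0 lists the PIQ6 (perceived impact of MRSE on everyday activities), the SF-12v2 (perceived general health) and an in-house questionnaire on symptoms and medical history, in three versions. None is described as measuring the amount of activity.
- **Interpretation.** Section 1.0 sets a specific aim to determine "whether statin therapy influences muscle morphology (in particular mitochondrial content and function"). Hypothesis 1 links reduced strength in MRSE patients to cell damage and perturbed mitochondria.

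**The concern.** Strength, endurance and mitochondrial enzyme content respond to training and to inactivity. The protocol restricts activity at entry, so it treats activity as relevant, but at a time when MRSE may already have changed it. A patient who was active before the statin and cut back because of pain can meet the limit, while an equally active patient without MRSE cannot. The groups may therefore differ in pre-statin activity.

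Pain is expected to fall between the two tests. MRSE patients may then become more active, whereas patients without MRSE have no pain-related loss to regain. A larger gain in the MRSE group could come from recovery of the muscle cell, from renewed activity, or from both. What is at stake is the mechanistic conclusion of Objective 1, including the biopsies meant to explain the functional change. If activity is never recorded, no later analysis plan can supply it.

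**Working it through.** The protocol gives no figure on this point to reproduce, so the check has two parts.

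**1. Does anything visible separate the two explanations?**

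- Entry limit: a single criterion with no re-check stated.
- Pairing of the non-MRSE group: statin and dosage only.
- Statin-naive controls: they show test-retest variability, but have no statin pain to lose.
- Questionnaires: the PIQ6 is a partial proxy for limitation, not a measure of hours.
- Section 5.0: one-way ANOVA on percent change, with no activity variable named. Covariates could be left to an analysis plan, but only if the data are collected.

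Nothing visible does so.

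**2. How large could the effect be?**

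Inputs from the protocol: 60 patients with MRSE, 30 without; two-sided alpha 0.05; pilot strength changes after withdrawal of 22±43% (extensors) and 17±28% (flexors), mean±SD, 9 patients.

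Assumptions, not in the protocol: 30% to 60% of MRSE patients become more active, and each of them gains 10% to 20% in strength over 2 months. The non-MRSE group does not shift, and there is no direct statin effect.

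Group shift = share more active × gain:

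- low: 0.30 × 10 = 3 points
- middle: 0.45 × 15 = 6.75 points
- high: 0.60 × 20 = 12 points

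Standard error of the group difference = SD × √(1/60 + 1/30) = SD × 0.2236:

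- SD 28: 6.26 points
- SD 35 (about midway): 7.83 points
- SD 43: 9.62 points

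Chance of a significant difference from a two-sided, two-sample t test with 60 + 30 − 2 = 88 degrees of freedom and noncentrality = shift / standard error:

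| Shift | SD | Noncentrality | Chance of p < 0.05 |
|---|---|---|---|
| 3 | 43 | 0.31 | 6.1% |
| 3 | 28 | 0.48 | 7.6% |
| 6.75 | 35 | 0.86 | about 14% |
| 12 | 43 | 1.25 | 23.5% |
| 12 | 28 | 1.92 | 47.4% |

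With no shift the chance is 5%. The low end is therefore close to no bias, and the high end needs the largest share, the largest gain and the smaller SD together.

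**The case against.** **The bias is possible, not shown.** A reader might infer that pain has already cut the activity of the enrolled patients and that deconditioning will be read as statin damage. The documents do not support that. The background sentence is a general remark that pain often alters activity; it says nothing about how much, or about these patients. The pilot reports decreased pain, not resolved pain. That patients without MRSE who pass the limit are sedentary by habit is inference. This objection stands.

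**The magnitude is assumed.** Neither the share becoming more active nor the gain has a source in the protocol, and the middle of the range gives only about 14%. This also stands; the figures show scale only.

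**Activity is a mediator.** Inactivity caused by statin pain is itself a consequence of the statin. The first specific aim asks whether a loss of strength and endurance can result from treatment, and Hypothesis 2 says that stopping improves function. Both can be answered as total effects whether or not activity lies on the pathway. This stands and narrows the point to mechanism. It also means that adjusting for activity change can remove part of the real effect.

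**Unseen material.** The Appendix 3 questionnaires may ask about activity, and participant instructions may sit in text not shown. If so, part of the fix is already in place.

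**Scope.** The vitamin D comparison is randomised, so activity at randomisation is balanced in expectation. The point concerns Objective 1.

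**What does not fall.** Nothing visible holds activity constant or records it between the two tests, and the PIQ6 follows perceived impact, not amount.

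**Conclusion.** The point holds for the mechanistic reading of Objective 1: the second specific aim, the biopsy comparison (20 patients with MRSE, 10 without) and Hypothesis 1. As visible, the design cannot tell a direct statin effect on muscle from disuse and reconditioning. Under the assumed shift of 3 to 12 points, a difference between 60 and 30 patients would be significant in about 6% to 47% of trials with no direct effect; the true size is unknown.

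It would go too far to conclude that Objective 1 fails, or that the vitamin D trial is biased. The total effect of stopping the statin (first specific aim, Hypothesis 2) stands, as does the randomised comparison. This is an inexpensive improvement that should be made before data collection. Confidence is medium, because the size is assumed and the questionnaires are not shown.

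**What to change.** In Objective 1, Functional assessment and blood samples:

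1. Ask all participants, including the statin-naive controls, to keep leisure activity unchanged between tests.
2. Record weekly hours of leisure activity at each functional-test visit. Record usual pre-statin hours once at screening, as a descriptive variable.
3. Next to the unadjusted primary result, report a supportive analysis of the change in strength and mitochondrial markers that takes change in activity hours into account. Label it as a mediator (direct-effect) analysis.

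Pre-statin activity should not become an eligibility rule. If 30% to 60% of MRSE patients really were active beforehand, such a rule would remove about that share of otherwise eligible patients; if only a few were, the bias would be small.

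Cost: a few added questions at existing visits, one instruction and one secondary analysis. The supportive analysis may take out part of the true total withdrawal effect, so it must not replace the unadjusted result. If the Appendix 3 questionnaires already record activity hours, step 2 only needs to be stated in the protocol.

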**Research Proposal**

---

prescribed chronic medications are compliant [9]. Statins are no exception to this observation. The proportion of patients in the province of Quebec who were 80% adherent over 2 years of statin treatment was less than 60% [10]. Of 100 patients starting statins for the primary prevention of coronary events, 44 will have discontinued therapy before any clinical benefit can be expected [11]. We suspect that statin-induced MRSE contribute significantly to this phenomenon, although this has not been studied.

***Statin-induced MRSE remain an underappreciated phenomenon, and very little is known on their effects on patient compliance or on how to prevent or reduce these symptoms.***

**Statins, muscle strength, and exercise performance.** Very few data are available on the effects of statins on muscle function. The authors of a recent review [12] examined published reports on the effects of statins on skeletal muscle strength and exercise performance and identified only 6 studies with data on the effects of statins on muscle strength, and 9 with data on exercise performance. Their main conclusions were that “there is insufficient data to determine if statins affect muscle strength and exercise performance” and that “there is suggestive evidence that these drugs may reduce muscle strength in older patients and alter energy metabolism during aerobic exercise”. The paucity of data on these issues clearly warrants further studies. ***To our knowledge, no study has systematically examined the impact of statin-induced myalgia on muscle strength and endurance.***

Complicating matters further, a number of major confounders and technical problems are found in the few studies examining statin effects on muscle function. First, the characteristics of subjects under statins are often incomplete. For example, most of these studies do not distinguish between patients with or without statin-related myalgia. Also, in many of the studies, the precise methods used to assess muscle function are either poorly described, or are subject to significant error and are inappropriate for small group studies.

The first study to examine the possible associations of statins and muscle strength was that of Phillips *et al.* [13]. Hip flexion and abduction strength was measured in 4 patients with muscle myopathy, but with normal creatine kinase and statin blood levels. Compared to measures while off statins, statin use by these patients resulted in ~25% and ~19% decreases in hip flexion and abduction strength, respectively.

Using data from the Tasmanian Older Adults Cohort Study (TASOAC), Scott *et al.* [7] reported that statin users aged 50-79 years had significantly lower mean leg strength (isometric muscle strength of the quadriceps and hip extensors assessed with a dynamometer) than non-users. Over time, statin users also lost more strength and muscle mass compared to those who had stopped statin therapy after first entering the prospective study. These data suggest that statin use reversibly decreases muscle strength in older adults. In the observational Hertfordshire Cohort Study, no effect of statins on handgrip strength was noted in a group of men and women aged 59-73 [14]. In both of these studies no distinction was made between statin users with or without MRSE.

In terms of exercise capacity, data from published studies appear to be contradictory. A prospective study on the effects of 12 weeks of high-dose statin therapy (simvastatin 80 mg/day) in 10 patients aged 55-76 yrs failed to show any change in aerobic capacity, endurance, oxygen kinetics or muscle strength (chest press and leg press 1-RM) [15]. None of the subjects in this study reported symptoms of myalgia or cramps, leading the authors to conclude that in the absence of myalgia or myopathic symptoms, high-dose simvastatin treatment did not impair exercise capacity in hyperlipidemic older individuals.

In patients with stable congestive heart failure, atorvastatin treatment for 8 weeks improved flow-dependent brachial vasodilation and increased average 6 min walking distance by about 10% [16]. In patients with peripheral arterial disease, atorvastatin [17] and simvastatin [18] improved pain-free walk time when compared to placebo, presumably by improving the endothelial vasodilatory response to exercise. A recent meta-analysis [19] concludes that statins are the most efficient pharmacotherapy to improve mean walking distance in patients with intermittent claudication caused by peripheral vascular disease. Again, no information on MRSE status of the patients in these studies is available.

---
